**Figure 2 F2:**
[figure not shown]
Sampling flowchart of CHCN-BTH.

### Ethical Consideration

This study was approved by the ethics committee of the Center of Disease Control (IRB2017-003, CYCDPCIRB-20170830-1) and Capital Medical University (2018SY81). Written informed consent was obtained from all participants prior to the baseline survey.

### Participants and Selection Criteria

To establish a community-based cohort study in the BTH area, participants will be eligible for the study if they meet the following inclusion criteria: (1) ≥18 years old; (2) living in the local area for more than 3 years; (3) can complete the investigation independently or with the help of investigators; and (4) signed informed consent. Participants were excluded from the study if they met any of the following exclusion criteria: (1) pregnant women; (2) patients with major physical or mental disabilities that might invalidate informed consent or the interview outcomes according to clinical judgment; and (3) unable to complete the baseline survey even with the help of investigators. All of the participants meeting the above criteria will undergo a physical examination after fasting for 8 h and be recruited for the CHCN-BTH study.

### Measurements

Participants were required to undergo fasting blood sampling, blood pressure (BP) and body composition measurements first. All of these tests were conducted after fasting for at least 8 h. Then, the participants will undergo measurements of bone mineral density and electrocardiography (ECG) and have a face-to-face interview to complete the questionnaire. In addition to the information about the disease history in the questionnaire, lung function measurements were performed in participants except for those meeting the following exclusion criteria: (1) underwent chest, abdomen, or eye surgery in the last 3 months; (2) had a heart attack (angina pectoris, MI, or severe arrhythmia) in the last 3 months; (3) systolic BP (SBP) ≥140 mmHg or diastolic BP (DBP) ≥90 mmHg on the day of the survey; (4) history of tuberculosis, disinsertion, tumor, schizophrenia, or cognitive disorder; or (5) pregnant or lactating women. Table 1 provides an overview of all study assessments. A flowchart of the field survey is shown in Figure 3.

**Table 1 T1:** Study timeline and assessment of the CHCN-BTH.

	**Baseline**	**Follow-up^£^**	**Repeated measurements^*^**
**Baseline characteristics**			
Sociodemographic data	X	X	X
Personal and family disease history	X		
Lifestyle behaviors	X	X	X
Indoor air pollution exposure	X		X
Mental health	X		X
Blood pressure	X	X	X
Body composition	X		X
Electrocardiography	X		X
Bone mineral density	X		X
Lung function	X		X
Grip strength	X		X
Oxygen saturation	X		X
Serum markers	X	X	X

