**Figure 3 F3:**
[figure not shown]
Flowchart of the baseline survey in CHCN-BTH.

Suitable places for the field survey were selected after consideration of the space needed for the survey instruments and the waiting space needed for the survey subjects. For example, we selected community healthcare centers or temporarily requisitioned schools near community healthcare centers as survey places. Face-to-face interviews will be performed using a uniform questionnaire. To ensure the accuracy of the questionnaire information, all questionnaires will be verified by the inspectors. The questionnaire includes five sections: sociodemographic characteristics, familial and personal medical history, lifestyle behaviors (including drinking, smoking, physical exercise), pollutant exposure (passive smoking condition and air pollution exposure condition), and psychological conditions. Current smoking was defined as smoking at least one cigarette per day in the last 6 months. Former smoking was defined as smoking less than one cigarette per day for at least 6 months. Alcohol drinking was defined as accumulatively drinking wine/liqueur more than 250 g/year or drinking beer more than 5 L/year (24). Physical exercise was defined as participating in moderate or vigorous activity for at least 30 min each time and at least once per week. Information on psychological conditions was collected using the Depression, Anxiety and Stress Scale-21 (25, 26). The scale includes three subscales, and each subscale contains seven items. The details of the questionnaire are shown in Table 2.

**Table 2 T2:** Sections and topics of the questionnaire.

**Type of data**	**Components**
Sociodemographic characteristics	Sex, age, ethnicity
	Residence address
	Cellphone number
	Personal income, education, occupation
	Menstrual history
Personal and family disease history	Hypertension (date of diagnosis, medication)
	Diabetes (date of diagnosis, medication)
	Cardiovascular disease (date of diagnosis, medication)
	Respiratory disease
	Gastrointestinal disease
	Cancer
	Others
Lifestyle behaviors	Tobacco use and smoking
	Alcohol consumption
	Labor intensity
	Physical activity/frequency
Outdoor exposure	Outdoor activity/frequency
	Window opening frequency
	Protective measurements during smog:
	Stay indoors/mask wearing/usage of air purifier
Indoor air pollution exposure	Passive smoking
	Cooking fuel type, cooking frequency
	Cooking habits:
	Kitchen door opening/usage of smoke extractors

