	Winter heating fuel type
Mental health	Depression (normal: ≤ 9; mild: 10–13; moderate: 14–20; severe: 21–27; serious severe: ≥28)
	Anxiety (normal: ≤ 7; mild: 8–9; moderate: 10–14; severe: 15–19; serious severe: ≥20)
	Stress (normal: ≤ 14; mild: 15–18; moderate: 19–25; severe: 26–33; serious severe: ≥34)

Subjects will be asked to bring the packaging of their most recent medications, as well as any medical records from secondary or tertiary hospitals, before they participate in the baseline survey. When conducting the face-to-face questionnaires, investigators with medical backgrounds will check the participants' medical records and their medicine packages, and then they will record the participants' disease history and medication history according to their findings. For self-reported incident diseases during the follow-up, the staff of the community health service center will collect the patient's medical information, including hospital, hospital admission time, the results of medical examinations, and diagnoses. The Clinical Event Committee (CEC) comprised three to five physicians working in tertiary hospitals with relevant specialties (hypertension, diabetes, cardiovascular disease, chronic obstructive pulmonary disease, and cancer). CEC members will ascertain the outcome events according to the medical records provided by the participants or collected by community healthcare workers.

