### Follow-Up

Community-based participants will be followed up every 2 years. All of the participants will be followed up by telephone-based interviews. Several methods will be used to achieve the goal that the overall follow-up rate should be more than 90%. Ways to guarantee a high follow-up rate are as follows: (1) For each participant, we will conduct telephone interviews on both workdays and weekends to ensure they can answer the telephone at least once. (2) For participants who cannot be contacted by telephone, a household survey will be conducted according to their baseline home address. (3) For participants who could not be contacted by telephone or household surveys, medical records in community healthcare centers will be acquired to confirm their health status and to collect information on BP, weight, and fasting blood glucose. (4) Death surveillance is generally based on the Disease Surveillance Point (DSP) system. For places not covered by DSPs, community healthcare centers will help to collect medical certificates of death. Photos of death certificates will be named “ID+name of participants” and collected by the research group. (5) Subjects will be deemed lost to follow-up if they cannot be contacted by telephone or household survey, and their medical or death records are not accessible. Information on home address changes, self-reported disease status, and its potential determinants will be collected in the follow-up survey through telephone interviews or household surveys. The expected proportion of participants lost to follow-up is <10%. We will recruit new participants in their community to replace the lost participants, matching by age and sex.

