Among the participants interviewed by telephone in the follow-up survey, we will randomly select 1% to conduct the survey again at each survey site. If the proportion of inconsistent information from the above two surveys is >10%, all of the participants at that survey site will be resurveyed. For all the community-based participants, BP, disease status, and serum markers (fasting glucose, total cholesterol, triglyceride, low-density lipoprotein cholesterol, and high-density lipoprotein cholesterol) will be accessed through medical records in community hospitals during follow-up survey. The minimum proportion of repeated measurements among community participants will be 20% at each follow-up. All participants will be examined after five rounds of follow-up surveys. For participants who undergo employee physical examinations, serum markers and physical examination exactly the same as baseline will be examined every 2 years. The follow-up procedure is shown in Figure 4.

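### As scheduled, medication is not collected after baseline, so later changes in blood pressure, glucose and lipids cannot be reliably separated from treatment started during follow-up

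*Protocol article*

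**What the plan says.** The Measurements section presents Table 1 as covering all of the study's assessments. Its row "Personal and family disease history" has a mark under Baseline and blanks under Follow-up and Repeated measurements. Blood pressure and serum markers are marked in all three columns.

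Table 2 shows what that questionnaire section contains. Its first entry reads "Hypertension (date of diagnosis, medication", and the diabetes and cardiovascular disease entries have the same form. The check of medicine packages also belongs to baseline: participants bring packaging "as well as any medical records from secondary or tertiary hospitals, before they participate in the baseline survey".

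The data sources after baseline are described as follows:

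- Incident disease (Measurements): community staff collect medical information "including hospital, hospital admission time, the results of medical examinations, and diagnoses".
- Interview or household visit (Follow-Up): "Information on home address changes, self-reported disease status, and its potential determinants will be collected in the follow-up survey".
- Community records (Follow-Up): "BP, disease status, and serum markers (fasting glucose, total cholesterol, triglyceride, low-density lipoprotein cholesterol, and high-density lipoprotein cholesterol) will be accessed through medical records".
- Employee participants (Follow-Up): "serum markers and physical examination exactly the same as baseline will be examined every 2 years".

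Intermediate phenotypes are among the Outcomes of Interest. The Statistical Plan relates pollutants to physiological indicators and uses trajectory analysis for changes in risk factors. The Discussion says that the 20% repeatedly measured make trajectory analysis possible.

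**The concern.** Treatment is not started at random. The people whose blood pressure, glucose or LDL cholesterol rises most are the most likely to be diagnosed and treated, and their later values then fall because of the drug. Without a record of current treatment, a treated decline and an untreated improvement look the same in the data.

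Two kinds of analysis are exposed. In trajectory analysis, a group labelled as improving may contain many treated high-risk people and show a high event rate for that reason. In longitudinal models of pollution and physiological indicators, an effect on blood pressure, glucose or lipids would be masked more where treatment is more common. The sites supply the pollution contrast, and the Sampling Methods section says that cities were selected partly on the quality of medical services. Treatment uptake could therefore differ along the same lines as exposure.

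This is a matter of data capture. An analysis plan written later can choose how to handle treated values, but it cannot restore treatment dates that were never collected.

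**Working it through.** The point rests on reading the schedule against the data lists. The article gives no figure to reproduce.

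**Step 1: the schedule.** Table 1 has 13 rows under baseline characteristics. The disease-history row is the only one with no mark in either later column. Lifestyle, indoor exposure and mental health, which come from the same questionnaire, are all marked for repeated measurement. The section that holds medication is not.

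**Step 2: whether another source fills the gap.**

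| Source after baseline | Items named | Drugs named? |
|---|---|---|
| Incident-disease information | hospital, admission time, examination results, diagnoses | no |
| Interview or household visit | address change, disease status, determinants | no |
| Records for participants who cannot be reached | health status, blood pressure, weight, fasting glucose | no |
| Community record extraction | blood pressure, disease status, five serum markers | no |
| Employee examinations | serum markers, physical examination | no |
| Outcome rows of Table 1 | six disease groups, death and its cause | no |

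The last row helps in part. It shows that hypertension or diabetes was diagnosed, but not whether or when a drug was started. It has no lipid entry.

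**Step 3: the full repeat.** A footnote to Table 1 says that all measures will have been repeated after five follow-ups. At 2-year intervals this is 5 × 2 = 10 years. The footnote belongs to the column in which the disease-history row is blank. Even on a generous reading, one repeat within ten years would not, as a record of current use, date treatment starts between the 2-yearly values.

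**Step 4: who is affected.** The minimum repeat is 20% of community participants per round, or 0.20 × 30,000 = 6,000. The 6,000 employee participants are examined every 2 years. For the remaining community participants, 2-yearly values come from records. The article does not say that those values enter the trajectory analysis.

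**Step 5: illustration of size.** Let u be the proportion starting antihypertensives during follow-up and d the mean fall in systolic pressure when treated. The shift in the mean is u × d. Both inputs are assumptions, since the document gives neither.

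- Low: 0.10 × 8 = 0.8 mmHg.
- High: 0.20 × 12 = 2.4 mmHg.
- Two sites whose uptake differs by 10 percentage points (also assumed), with d = 10: 0.10 × 10 = 1 mmHg. With d from 8 to 12 the range is 0.8-1.2 mmHg.

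The shift falls on the treated, who tend to have the worst untreated values, so its effect on trajectory groups is not described by the mean alone.

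**The case against.** The strongest reply is that a blank cell beside a history item does not prove that medication goes unrecorded. Past and family history is naturally a baseline item, and later disease moves to the outcome rows. The text elsewhere names medication history separately from disease history. Table 1 also does not mirror Table 2 exactly: outdoor exposure is a Table 2 section with no row in Table 1, yet it is collected. The list for incident disease is open-ended, the interview covers determinants of disease, and the Discussion promises that medical information will be updated and that records will be renewed every 2 years. The follow-up form is not shown.

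Part of this stands. A reader might infer that medication is certainly never seen after baseline. The document does not support that, because the record updates could include prescriptions. But these statements are general. None names drugs, and none overrides a printed schedule and an itemised extraction list.

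A reader might also infer that 2-yearly values from the whole cohort drive the trajectory analysis, or that the incidence and mortality results are distorted in the same way. Neither is supported. The Discussion ties trajectories to the repeatedly measured 20%. The sentence on generalized additive mixed models pairs physiological indicators with prevalence, which fits a baseline analysis as well. The Cox models take incident disease as their endpoint, not later blood pressure, glucose or lipid values.

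Finally, analysts could censor or stratify at diagnosis. That is usable but imperfect, because treatment may start later than diagnosis or not at all, and people already diagnosed at baseline may start or change drugs without any new diagnosis.

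**Conclusion.** The point holds in conditional form. As scheduled, medication is not collected after baseline, and no follow-up list names it. Unless prescriptions are also taken from the updated records, changes in blood pressure, glucose and lipids cannot be reliably separated from treatment started during follow-up. The affected work is the trajectory and longitudinal analysis of these values, at least in the repeatedly measured subgroup.

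The size of the bias is unknown. The 0.8-2.4 mmHg range is illustrative and is simply the product of assumed uptake and drug effect. A reader might take the 1 mmHg site contrast as a finding about these cities. It is not: selecting sites for differing medical services makes unequal uptake plausible but does not measure it. The correction is worth making because it is cheap and because missing treatment dates are hard to recover later.

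**What to change.** - In Table 1, separate medication from disease history and give it its own row, marked under Baseline, Follow-up and Repeated measurements. Record current use and start date for antihypertensive, glucose-lowering and lipid-lowering drugs.
- Ask these items in the 2-yearly interview, and ask employee participants the same at their 2-yearly examination.
- Add medication to the items extracted from community records in the Follow-Up section. If the general record update already captures prescriptions, say so there.
- State that treatment will be treated as time-varying in models of blood pressure, glucose and lipids. The method can be left to the statistical analysis plan.

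The cost is a few extra questions in a call that already takes place and one more field from records that are already opened. The change concerns what is recorded and does not touch anyone's care.

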**Outcome measures**			
Hypertension		X	X
Diabetes		X	X
Ischemic heart disease		X	X
Cerebrovascular disease		X	X
Chronic obstructive pulmonary disease		X	X
Cancer		X	X
Death/cause of death		X	X

£ *All the participants will be followed up every 2 years; the proportion of loss to follow-up will be restricted to <10%*.

* *A subgroup of baseline participants will be selected to do repeated measurement every 2 years; the minimum proportion of repeated measurements will be 20% in each time of follow-up. All measures will be repeated after five patient follow-ups*.

**Figure 3 F3:**
[figure not shown]
Flowchart of the baseline survey in CHCN-BTH.

Suitable places for the field survey were selected after consideration of the space needed for the survey instruments and the waiting space needed for the survey subjects. For example, we selected community healthcare centers or temporarily requisitioned schools near community healthcare centers as survey places. Face-to-face interviews will be performed using a uniform questionnaire. To ensure the accuracy of the questionnaire information, all questionnaires will be verified by the inspectors. The questionnaire includes five sections: sociodemographic characteristics, familial and personal medical history, lifestyle behaviors (including drinking, smoking, physical exercise), pollutant exposure (passive smoking condition and air pollution exposure condition), and psychological conditions. Current smoking was defined as smoking at least one cigarette per day in the last 6 months. Former smoking was defined as smoking less than one cigarette per day for at least 6 months. Alcohol drinking was defined as accumulatively drinking wine/liqueur more than 250 g/year or drinking beer more than 5 L/year (24). Physical exercise was defined as participating in moderate or vigorous activity for at least 30 min each time and at least once per week. Information on psychological conditions was collected using the Depression, Anxiety and Stress Scale-21 (25, 26). The scale includes three subscales, and each subscale contains seven items. The details of the questionnaire are shown in Table 2.

**Table 2 T2:** Sections and topics of the questionnaire.

**Type of data**	**Components**
Sociodemographic characteristics	Sex, age, ethnicity
	Residence address
	Cellphone number
	Personal income, education, occupation
	Menstrual history
Personal and family disease history	Hypertension (date of diagnosis, medication)
	Diabetes (date of diagnosis, medication)
	Cardiovascular disease (date of diagnosis, medication)
	Respiratory disease
	Gastrointestinal disease
	Cancer
	Others
Lifestyle behaviors	Tobacco use and smoking
	Alcohol consumption
	Labor intensity
	Physical activity/frequency
Outdoor exposure	Outdoor activity/frequency
	Window opening frequency
	Protective measurements during smog:
	Stay indoors/mask wearing/usage of air purifier
Indoor air pollution exposure	Passive smoking
	Cooking fuel type, cooking frequency
	Cooking habits:
	Kitchen door opening/usage of smoke extractors
	Winter heating fuel type
Mental health	Depression (normal: ≤ 9; mild: 10–13; moderate: 14–20; severe: 21–27; serious severe: ≥28)
	Anxiety (normal: ≤ 7; mild: 8–9; moderate: 10–14; severe: 15–19; serious severe: ≥20)
	Stress (normal: ≤ 14; mild: 15–18; moderate: 19–25; severe: 26–33; serious severe: ≥34)

Subjects will be asked to bring the packaging of their most recent medications, as well as any medical records from secondary or tertiary hospitals, before they participate in the baseline survey. When conducting the face-to-face questionnaires, investigators with medical backgrounds will check the participants' medical records and their medicine packages, and then they will record the participants' disease history and medication history according to their findings. For self-reported incident diseases during the follow-up, the staff of the community health service center will collect the patient's medical information, including hospital, hospital admission time, the results of medical examinations, and diagnoses. The Clinical Event Committee (CEC) comprised three to five physicians working in tertiary hospitals with relevant specialties (hypertension, diabetes, cardiovascular disease, chronic obstructive pulmonary disease, and cancer). CEC members will ascertain the outcome events according to the medical records provided by the participants or collected by community healthcare workers.

Indoor pollutant exposures will also be obtained from face-to-face interviews, including asking about passive smoking, cooking fuel, cooking habits, and winter heating fuel. Ambient air pollutants are generally estimated by the following procedure: (1) annual concentrations of particles with aerodynamic diameters of no >2.5 μm (PM_2.5_) will be estimated with a machine learning method at a resolution of 0.1° × 0.1° using high-dimensional expansion of numerous predictors (including ground-monitored PM_2.5_ data, satellite-derived aerosol optical depth and other satellite covariates, meteorological variables, and chemical transport model simulations). (2) Concentrations of particles with aerodynamic diameters of no >10 μm (PM_10_), nitrogen dioxide (NO_2_), SO_2_, CO, and O_3_ will be collected using air monitoring stations. In each of the study districts, there will be more than one air monitoring station. Continuous hourly concentrations will be gathered. The daily average concentrations of PM_2.5_, PM_10_, SO_2_, NO_2_, and CO at each station will be used only if >20 of the 24-hourly measurements are available. For O_3_, at least six hourly concentrations of O_3_ per day will be needed to calculate the 8-h average concentration of O_3_. The air pollutant concentration measurements are valid and are conducted in accordance with the China Ambient Air Quality Standards (GB 3095-2012). Information on outdoor activity, window opening frequency, and protective measurements during smog are also included in the questionnaire to evaluate the effect of ambient air pollutants more accurately.

Physical examinations will include assessments of BP, heart rate, grip strength, oxygen saturation, body composition, bone mineral density, ECG, and lung function. BP will be measured with a digital sphygmomanometer (OMRON HEM-907, Japan) after resting in a seated position for at least 10 min. Measurements will be recorded three times with 1-min intervals, and the mean SBP and DBP will be recorded. Body composition will be measured in the upright position after fasting and urinating with their arms naturally hanging by using a body composition analyzer (TANITA BC-420, Japan). Resting ECG will be performed in the supine position after sitting quietly for 5 min. A standard 12-lead ECG will be acquired digitally using a Mortara ECG machine (Mortara Eli 250c, Milwaukee, WI, USA) at a calibration of 10 mm/mV and a speed of 25 mm/s. Bone mineral density will be measured in a seated position using an Osteospace Pegasus ultrasound bone densitometer (MEDILINK, France). Bone mineral density measurements will be conducted on the participant's bare right ankle and foot by using a Pegasus device (MEDILINK, France). Lung function measurement (spirometry) will be conducted using a portable spirometer (CareFusion MasterScreen Pneumo, Germany) according to the guidelines issued by the American Thoracic Society (27). All physical examinations will be carried out by trained staff based on a standard manual, and all of the measurement equipment will be regularly calibrated. Details of the physical examination measurements are shown in Table 3.

**Table 3 T3:** Physical examination measurements and laboratory test.

**Measures**	**Measuring equipment**	**Variables**	**Times of measurements**
Blood pressure	OMRON HEM-907, Japan	Systolic pressure (SBP, mmHg), diastolic blood pressure (DBP, mmHg)	3
Body composition	TANITA BC-420, Japan	Height, cloth weight, weight, reference value of weight, fat mass rating (fat%), reference value of fat%, fat mass, reference value of fat mass, fat-free body mass, muscle mass, reference value of muscle mass, muscle mass rating, bone mass, reference value of bone mass, body water, reference value of the body water, the body water rating, reference value of the body degree, body mass index (BMI), standard weight, obesity degree, visceral fat rating, the basic metabolic rate, the basic metabolic rate, basal metabolism, metabolism age, and impedance	1
Electrocardiography	Mortara Eli 250c, Milwaukee, WI, USA	Heart rate, basic heart rhythm, PR interval, QRS complex, QT interval, QTc interval, P axis, and T axis	1
Bone mineral density	MEDILINK, France	Bone mineral density	
Lung function	CareFusion MasterScreen Pneumo Germany	Forced vital capacity (FVC), forced expiratory volume in 1 s (FEV1), peak expiratory flow (PEF), maximum midexpiratory flow (MMEF), and FEV1:FVC ratio	
Grip strength	JAMAR Kit, UK	Grip strength (kg)	2
Oxygen saturation	Masimo Red-57, USA	Oxygen saturation (%)	2
Serum markers	Beckman coulter chemistry analyzer AU5800	Aspartate aminotransferase (AST, U/L), alanine aminotransferase (ALT, U/L), γ-glutamyl transferase (GGT, U/L), urea (mmol/L), creatinine (CrE, μmol/L), uric acid (UA, μmol/L), fasting plasma glucose (FBG, mmol/L), cholesterol (TC, mmol/L), triglycerides (TG, mmol/L), high-density lipoprotein cholesterol (HDL-C, mmol/L), low-density lipoprotein cholesterol (LDL-C, mmol/L), hsCRP (mg/L), and Lp(a) (mg/L)	1

Fasting blood samples will be collected into a 2% EDTA Vacutainer and a coagulation-promoting Vacutainer. After centrifugation and aliquoting, four cryovials (including two plasma and two blood cell samples) will be filled from the 2% EDTA Vacutainer, and the serum samples from the coagulation-promoting Vacutainer will be separated into two cryovials. All of the above samples will be kept in an insulated box with ice packs to maintain their temperature at 0–4°C and transported to the local Center of Disease Control within 4 h. After being stored at −20°C in the local CDC for a few days, the serum samples will be transported on dry ice to Beijing Hepingli Hospital to test for serum markers. Serum markers will be tested using a Beckman Coulter chemistry analyzer AU5800 in the clinical laboratory of Beijing Hepingli Hospital. By the end of the serum testing, 36,000 sample aliquots will be stored in two geographically separate −80°C archives: 6,500 sample in Chinese Academy of Medical Sciences, and 29,500 sample in Capital Medical University. In each storage site, four cryovials (including two plasma and two blood cell samples) for each participant will be stored in two separate −80°C fridges (28).

